#### Phase II trial

The primary endpoint is 2-year OS after salvage CIRT with concurrent chemotherapy. The secondary endpoints are local control, disease-free survival, and long-term toxicity and safety.

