#### Phase II trial: treatment at recommended dose to study efficacy

Once the MTD is determined in the phase I trial, this dose will be used as the recommended dose for the phase II trial. If MTD is not reached at 65 GyE, we will use 65 GyE as the recommended dose.

The primary endpoint of the phase II trial is OS after re-irradiation, at a median follow-up of 24 months. To evaluate the OS rate, all patients will be followed up for at least 12 months or until death. We estimate that 1 patient per week will be recruited to the trial, and a total of 40 patients (minus the number of patients treated at the recommended dose in the phase I trial) will be recruited over approximately 9 months. The phase II trial is expected to be completed in 24 months.

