#### Phase II trial

The primary objective of the phase II trial is to evaluate the actuarial 2-year OS rate (π) for patients with locally recurrent NPC who receive CIRT plus concurrent cisplatin-based chemotherapy. The 2-year OS rate for patients with locally recurrent rT3 or rT4 NPC range from 40% to 50% after IMXT or proton re-irradiation [5, 7].

This is the first study to address the efficacy of re-irradiation with CIRT plus concurrent cisplatin-based chemotherapy on locally recurrent NPC. We estimate that CIRT will improve 2-year OS rate by 20% to 70%, compared with IMXT or proton therapy. Thus, confirmatory analysis of the primary endpoint assesses the following test problem: H0: π ≤ 0.50 = π0 versus H1: π > 0.70. The same single-stage design will be used for the phase II trial [27]. The null hypothesis is defined by the true OS rate being 50%, and it will be tested against a one-sided alternative. A sample size of 37 patients will be required, and the null hypothesis will be rejected if 23 or more survivors are observed among 37 patients, with a median follow-up of 2 years. This design yields a type I error rate of 0.05 and a power of 0.8 if the true OS rate is 70%.

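### The phase II survivor count does not require each patient's 24-month status, and the stated schedule cannot give newly enrolled patients the planned 24-month median follow-up

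*Protocol article*

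**What the plan says.** The protocol article gives the endpoint under Objectives, Phase II trial: "The primary endpoint is 2-year OS after salvage CIRT with concurrent chemotherapy". Under Statistics, Phase II trial, it describes the target as an actuarial 2-year rate, with a null value of 50% and an alternative of 70%. The rejection rule there is a count. The null is rejected if 23 or more "survivors are observed among 37 patients, with a median follow-up of 2 years", with a claimed type I error of 0.05 and power of 0.8.

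The timetable is in the section on treatment at the recommended dose:
- Analysis point: "The primary endpoint of the phase II trial is OS after re-irradiation, at a median follow-up of 24 months".
- Minimum follow-up: "To evaluate the OS rate, all patients will be followed up for at least 12 months or until death".
- Accrual rate: "We estimate that 1 patient per week will be recruited to the trial".
- Accrual period: the patients "will be recruited over approximately 9 months".
- Duration: "The phase II trial is expected to be completed in 24 months".
- Phase I patients at the recommended dose count toward the total: "a total of 40 patients (minus the number of patients treated at the recommended dose in the phase I trial").

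The OS section starts the clock at pathologic confirmation of the recurrence and censors living patients at last follow-up.

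**The concern.** A binomial test of a 2-year rate needs a yes-or-no answer at 24 months for every patient in the denominator. A median of 2 years guarantees that only for about half of them, and a 12-month minimum lets the rest fall well short. The count has no term for a patient alive and censored at, say, 17 months.

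The timetable makes this a practical issue. Patients who enter over 9 months cannot have a 24-month median when the phase ends at month 24. One of the stated figures has to give way, and which one decides the error rate. This count is the trial's only formal efficacy test and there is no control arm, so the false-success probability should be fixed in advance.

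**Working it through.** **1. The plan's own figure.** With X ~ Binomial(37, π) and every status known at 24 months:
- cut-off 23: P(X ≥ 23 | 0.50) = 0.094 and P(X ≥ 23 | 0.70) = 0.887;
- cut-off 24: P(X ≥ 24 | 0.50) = 0.049 and P(X ≥ 24 | 0.70) = 0.807.

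The claimed 0.05 and 0.8 belong to a cut-off of 24, not the printed 23. That is a separate error. Results for both cut-offs are given below so that the two problems stay apart.

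**2. Follow-up under the timetable.** A patient who enters at month e (0 to 9) has 24 − e months at month 24: a range of 15 to 24 and a median of 24 − 4.5 = 19.5. At 1 patient per week the median for 37 patients is about 19.9. Essentially only the first patient reaches 24 months. The last one does so at 9 + 24 = month 33.

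**3. Share alive at month 24 under the null.** Assume exponential survival with S(24) = 0.50, so S(t) = 0.5^(t/24). Averaged over t = 15 to 24 this is 0.571, not 0.50.

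**4. Chance of a false success.** Each patient has an alive-probability S(tᵢ), with tᵢ capped at 24 months unless noted. The number alive is a sum of independent unequal Bernoulli variables, evaluated exactly for n = 37 with no phase I carry-over unless stated.

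| Scenario (true 2-year OS 50%) | ≥23 | ≥24 |
|---|---|---|
| All statuses known at 24 months | 0.094 | 0.049 |
| Cut-off at month 24, follow-up 15–24 months | 0.33 | 0.22 |
| Same, OS starting 1 to 4 months before entry | 0.26 to 0.14 | 0.16 to 0.08 |
| 24-month median met (19.5–28.5 months), status at 24 months or at cut-off if earlier | 0.133 | 0.074 |
| Same, literal count of those alive at the cut-off (no cap) | 0.096 | 0.051 |
| Month 24, 4 to 10 carried over with full follow-up, accrual kept at 9 months | 0.29 to 0.25 | 0.19 to 0.15 |
| Same, accrual at 1 per week, so shorter | 0.24 to 0.18 | 0.15 to 0.11 |

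The 1-to-4-month lead and the 4-to-10 carry-over are assumed ranges; the article gives neither figure.

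**5. Sensitivity to survival shape.** With a Weibull shape of 1.5 (deaths later, same 2-year rate), the month-24 figures rise to 0.48 (≥23) and 0.35 (≥24).

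**The case against.** The strongest reply is that the article never says patients alive at an earlier cut-off count as 2-year survivors. A reader might infer that from the count rule, but the text does not support it as a fact. The target is described as actuarial, living patients are censored at last follow-up, and Kaplan–Meier is named for OS in the phase I statistics. The intended estimate may handle censoring properly, with details in an analysis plan not shown here. This stands. What remains is that the only decision rule stated is a count with binomial error rates, and it does not follow from an actuarial estimate.

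Second, completion in 24 months is a forecast, whereas the 24-month median is stated twice as the analysis point. If the median governs, the added inflation is small. In a literal count, deaths after 24 months offset short follow-up almost exactly (0.096 against 0.094). A reader might infer that the endpoint is always biased upward, or that the error rate simply is 0.33. Neither is supported, because the larger values need a month-24 cut-off.

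Third, OS starts at pathologic confirmation, before entry, and some patients have induction chemotherapy. That lead time adds follow-up; about 4.5 months of it would bring half of the new patients to 24 months. The article gives no interval, and it also describes the endpoint as OS after re-irradiation, so the origin is not settled.

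Fourth, carried-over phase I patients may have longer follow-up. This reduces the problem without removing it. At 1 patient per week, about 18 of 37 would have to be carried over before half reach 24 months, which is unlikely with at most 25 phase I patients spread over dose levels.

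**Conclusion.** The point holds in two parts, neither of which needs a modelling assumption. The stated rule tests a 2-year rate without requiring 24-month status and makes no provision for earlier censoring. The stated accrual period, duration and median follow-up also cannot all hold for newly enrolled patients.

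The consequence is an error rate that the plan does not fix. Across the scenarios shown, with exponential survival, the chance of a false success runs from about 0.10 to 0.33 at the printed cut-off and from 0.05 to 0.22 at a cut-off of 24. The upper ends apply to an analysis at month 24 with no lead time and no carry-over. The lower ends apply to a literal count once the 24-month median is met. The correct comparators are 0.094 and 0.049. Setting 0.33 directly against 0.05 would charge the separate cut-off error to the follow-up problem.

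**What to change.** Preferred: do the primary analysis when the last patient has reached 24 months, about month 33 of phase II. Change the minimum follow-up from 12 months to 24 months or death, count survivors on status at 24 months, and restate the phase II duration. State one time origin for the 24 months. Counting patients lost before 24 months as non-survivors is a conservative option, not a necessity.

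Alternative, if the earlier date must be kept: drop the count. Estimate 24-month survival by Kaplan–Meier and declare success only if the one-sided 95% lower bound exceeds 0.50.

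Cost: the preferred route delays the primary result by about 9 months (33 − 24). It needs no extra visits, since follow-up is already scheduled every 3 months for the first 3 years. The Kaplan–Meier route keeps the date at the price of somewhat lower precision, and its power should be restated because the binomial figures no longer apply. Neither route corrects the cut-off of 23, which needs its own change if a count is retained.

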### Inclusion and exclusion criteria

For this trial, all patients with a confirmed diagnosis of locally recurrent NPC will be evaluated and screened. Inclusion and exclusion criteria are listed in Table 2.

**Table 2 Tab2:** Inclusion and exclusion criteria for the phase I/II CIRT plus chemotherapy dose escalation trial for NPC

Inclusion criteria	Exclusion criteria
Pathologically and/or clinically confirmed locally recurrent NPC diagnosed more than 12 months after completion of initial IMXT Completed a definitive course of IMXT to a total dose of ≥66 Gy Age ≥18 and <70 years KPS score ≥70 Ability to understand the trial protocol, including the aims, methods, and consequences Willingness to provide written informed consent before enrollment in the trial Willingness to receive the study treatment, including CIRT and cisplatin-based concurrent chemotherapy For women with childbearing potential, willingness to use adequate contraception	Presence of distant metastasis Recurrence diagnosed within 12 months after the completion of the previous IMXT course Technology used other than IMXT (or IMXT used with other techniques, such as brachytherapy or SRS) for the initial treatment Pregnant or lactating women Patients who have not recovered from severe toxicities of prior radiotherapy or chemotherapy Diagnosis of any type of cancer other than CIS of the cervix and basal cell or squamous cell carcinoma of the skin within the past 5 years Participation in other clinical trial(s) whose treatments may interfere with the conduct or outcome of this trial

*CIRT* carbon-ion radiotherapy, *IMXT* X-ray–based intensity-modulated radiotherapy, *KPS* Karnofsky performance status, *SRS* stereotactic radiosurgery, *CIS* carcinoma in situ

#### Concurrent chemotherapy

The administration of concurrent cisplatin-based chemotherapy will start on the first day of CIRT and will consist of weekly cisplatin (40 mg/m^2^) during CIRT for a maximum of 5 cycles. Chemotherapy at the full dose will be delivered, and no adjustment will be allowed unless grade 4 chemotherapy-induced toxicities occur. The start of chemotherapy can be postponed if a patient’s neutrophil count drops below 2000/µL or the platelet count drops below 100,000/µL. Chemotherapy can be suspended if a patient’s creatinine clearance rate is less than 50 mL/min.

#### Other medications

Prescription medication required for the treatment of medical conditions other than NPC is allowed during the phase II trial. However, any treatments not related to the trial must be discussed with and thoroughly reviewed by the principal investigator prior to a patient’s inclusion.

### Radiation therapy^1^

#### Treatment planning

Patients will be immobilized using an individual immobilization system for planning and treatment. Planning CT without contrast will be performed; MRI scans in the treatment position will be obtained, registered, and fused with a planning CT.GTV is defined as the gross disease seen on the planning CT, area of contrast enhancement on T1-weighted MRI, and/or lesion(s) with high standardized uptake value observed on fluoro-d-glucose-PET/CT (optional).Clinical target volume (CTV) is defined as the GTV plus a 3 to 5-mm margin. The CTV for subclinical disease will be delineated based on the treating physician’s clinical judgment for potential subclinical disease.Planning target volume (PTV) will be added depending on individual factors such as patient positioning reproducibility and/or beam angles chosen and will range from 3 to 6 mm.

Critical OARs, including the brain stem, optic nerve, optic chiasm, temporal lobes of the brain, and eyes, will be contoured. A dose discount to OARs from the initial radiation course will be uniformly set at 70%; thus, 30% residual doses will be used to calculate the limiting dose to the OARs. Dose limitations of OARs will be controlled according to those reported by Emami et al. [26].

CIRT planning will be performed using the Syngo treatment planning system (Siemens; Erlangen, Germany), including biologic plan optimization. BED distributions will be calculated using the generally accepted an α/β ratio of 9 for NPC and an α/β ratio of 2 for late-responding tissues (generally presented as late toxicity).

#### Dose prescription for CIRT

Re-irradiation using intensity-modulated CIRT will be delivered using the IONTRIS raster scan system (Siemens Aktiengesellschaft, Munich, Germany). Six dose levels and the estimation of pDLT of each level are detailed in Table 1. A daily dose of 2.5 GyE will be delivered up to the total dose for all levels and be given concurrently with chemotherapy (see “Chemotherapy” above). After the MTD is determined or if the treatments to 65 GyE are safely delivered, the delivered dose (or 65 GyE) will be defined as recommended dose and used as the prescribed dose in the phase II stage of the study.

Ninety-five percent of the isodose line should cover the CTV for gross tumor (i.e., GTV plus 3–5 mm), and 90% of the dose line should cover the PTV for gross disease. The CTV for other subclinical disease, if applicable, will be irradiated to 90% of the assigned dose level.

Dose specification is based on BED, because the RBE of CIRT differs significantly from photon therapy. Therefore, the unit used for dose prescription is the iso-effective dose GyE daily for 5 fractions per week at 2 Gy per fraction.

#### Treatment planning and delivery

 The techniques of planning and delivery of intensity-modulated CIRT using raster-scanning technology were previously described [24]. Briefly, patients are irradiated once a day, 5 days a week. Treatment interruptions of more than 3 days are not allowed, unless severe adverse effects require such interruption. Weekend treatment will be provided if a break of 2 or more days occurred during the previous week. Treatment positioning prior to intensity-modulated CIRT will be verified by comparing orthogonal X-rays with the digitally reconstructed radiographs, and set-up deviations of more than 2 mm will be corrected. A typical treatment plan of a patient with locally recurrent NPC (rT3N0M0) is shown in Fig. 1.

**Fig. 1 Fig1:**
[figure not shown]
Typical treatment plan and dose distribution for intensity-modulated carbon-ion radiotherapy delivered using the raster-scanning technique in a patient with stage rT3N0M0 nasopharyngeal carcinoma with recurrence at the base of the skull. Transverse, sagittal, and coronal views are provided. The *red*, *orange*, *yellow*, and *blue shaded areas* represent 95%, 85%, 70%, and 30% isodose lines; the *red*, *green*, and *yellow*
*lines* represent gross tumor volume (GTV), GTV + 3 mm, and clinical target volume (CTV), respectively

### Assessment of efficacy parameters (see footnote 1)

#### Baseline documentation of “target” lesion

The target lesion is defined as the gross tumor that locally recurred in the nasopharynx or base of skull and that is scheduled for re-irradiation using CIRT. The sum of the longest diameter (LD) for the gross tumor will be measured and reported as the baseline sum LD. The baseline sum LD will be used as a reference to characterize the objective tumor.

#### Response to treatment

Response to CIRT will be recorded according to the Response Evaluation Criteria in Solid Tumors (RECIST) [26].

Evaluation of the target lesion by RECIST is summarized below.Complete response (CR): complete disappearance of the target lesions.Partial response (PR): at least a 30% decrease in the LD of the target lesion, taking the baseline sum LD as reference.Stable disease (SD): neither sufficient shrinkage to qualify for PR nor sufficient increase to qualify for PD, taking the smallest sum LD since the treatment started as reference.Progressive disease (PD): at least a 20% increase in the sum of the LD of the target lesion, taking the smallest sum LD recorded since the treatment (including neoadjuvant chemotherapy) started as reference.

Evaluation of non-target lesion(s)CR: disappearance of all non-target lesions and normalization of tumor marker level (not applicable for the current study).Incomplete response/SD: persistence of one or more non-target lesion(s) and/or maintenance of tumor marker level above the normal limits (not applicable for the current study).PD: appearance of one or more new lesions and/or unequivocal progression of existing non-target lesions.

Evaluation of best overall response

The best overall response will be considered the best extent of response recorded from the initiation of the study treatment until progression/recurrence of disease (taking as reference for PD with the smallest measurement of LD recorded since the treatment started). In general, the patient’s best response assignment will depend on the achievement of both measurement and confirmation criteria as follows.Patients will be classified as having “symptomatic deterioration” if, without disease progression, they experience an overall deterioration of general health status that necessitates discontinuation of chemoradiotherapy. Documentation of objective progression of the disease during and after the study treatment will be required.In some circumstances, it may be difficult to distinguish residual disease from normal tissue. When the evaluation of CR depends on this determination, it is recommended that the residual lesion be histologically investigated (by fine or core needle biopsy, for example) to confirm the CR status.

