### Follow-up after trial completion

#### Follow-up

After completion of the study treatment, all patients will be required to be followed up regularly, indefinitely or until death, according to our institutional follow-up protocol for head and neck cancers. The first and second follow-up will be scheduled at 1 and 3 months after the completion of radiotherapy, respectively. Unless otherwise clinically necessary, follow-up sessions will then be scheduled every 3 months in the first 3 years, every 6 months in the following 2 years, and annually thereafter. Each follow-up examination will include a complete history and physical examination, MRI or CT scans with contrast of those for the head and neck area, and blood tests (including complete blood counts, serum electrolyte levels, pituitary function, and liver/renal function), and EBV DNA copies. Whole-body PET/CT scans is optional but preferable over thoracic and/or abdominal CT scans, and bone scans if clinically indicated.

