Our previous work at the SPHIC showed that patients with locally recurrent NPC who received re-irradiation alone using intensity-modulated CIRT up to 57.5 GyE in 25 fractions tolerated it well [24]. Within 3 months after completion of CIRT, most patients achieved a PR or CR, without grade 2 or higher radiation-induced adverse effects. However, longer follow-up is needed to determine the likelihood of developing late CIRT-induced toxicities. A phase I/II clinical trial with the aims of determining the MTD of re-irradiation with CIRT and the efficacy of CIRT at the MTD is ongoing [24]. Induction chemotherapy may be used for the treatment of locally advanced NPC at recurrence to reduce the tumor burden and to control subclinical distant metastases. However, chemotherapy is not being used concurrently with CIRT.

Concurrent chemotherapy with definitive radiotherapy has been proven effective in the treatment of NPC [18]; however, its effectiveness in the management of locally recurrent NPC has not been confirmed. In addition, the use of concurrent chemotherapy plus high-LET irradiation, such as CIRT, for the purpose of radiosensitization has never been addressed. Therefore, after the initiation of the previous phase I/II trial that focused on CIRT alone and after completing the accrual of patients for the first dose level (57.5 GyE with a daily fraction dose of 2.5 GyE), we initiated this trial to address the safety and effectiveness of CIRT plus concurrent cisplatin-based chemotherapy. Although all patients completed 57.5 GyE without experiencing any moderate or severe adverse effects (unpublished data), the starting dose used in the current study was 55 GyE, which is one echelon lower than the starting dose used in our CIRT-alone trial. This was done to avoid possible severe adverse effects from the potential synergistic effects of concurrent chemotherapy plus CIRT.

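### Target-lesion progression is a purely relative 20% rise over the smallest measurement, so reading error alone can meet it on small residuals; a minimum change in mm would help (minor, secondary endpoints only)

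*Protocol article*

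**What the plan says.** In its section on response to treatment, the protocol article introduces its criteria with the words "Evaluation of the target lesion by RECIST is summarized below". No RECIST version is named. Target-lesion progressive disease is defined as "at least a 20% increase in the sum of the LD of the target lesion". The comparison for that increase is made by "taking the smallest sum LD recorded since the treatment (including neoadjuvant chemotherapy) started as reference". The threshold is thus relative only, and the reference is a running minimum. No absolute minimum change is given.

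The same section says that "best response assignment will depend on the achievement of both measurement and confirmation criteria as follows". What follows is a category for symptomatic deterioration, the sentence "Documentation of objective progression of the disease during and after the study treatment will be required", and a recommendation to biopsy when a complete response is in doubt. None of these asks for a repeat scan before progression is called.

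In the section on baseline documentation of the lesion, the target is the recurrent gross tumour, so the sum may be a single diameter. On timing, visits fall at 1 and 3 months after radiotherapy, and "follow-up sessions will then be scheduled every 3 months in the first 3 years", each with MRI or CT of the head and neck.

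**The concern.** A percentage of a small number is a small number. Twenty percent of a 10 mm nadir is 2 mm, and of a 5 mm nadir 1 mm. A residual that does not change but is read as 10, 9, 10 and 11 mm is progressive at the fourth reading, because 11/9 = 1.22. Each further scan is another test against the threshold and may also lower the reference, so false calls accumulate over follow-up.

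The endpoints exposed are secondary: tumour response and local progression-free survival in phase I, and local control and disease-free survival in phase II. A false call counts as an event that did not happen, and it ends the best-response window early. The error falls mostly on patients whose tumours shrank well without vanishing, because they have the smallest measurable nadirs.

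**Working it through.** The article gives no figure that rests on this rule, so there is nothing to reproduce. The check asks how often reading error alone meets the rule.

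**Inputs from the article.** Progression if a reading is at least 1.2 times the smallest earlier reading. Scans at months 1, 3, 6, 9, 12, 15, 18, 21 and 24, which makes 9.

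**Assumptions, not in the article.** A truly stable residual of length L, normal reading error with SD s, shown range 0.5 to 1.5 mm, and either independent errors or a correlation of 0.5 between readings of the same lesion.

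**Hand check.** Progression is called if any later reading is at least 1.2 times any earlier one. Nine scans give 9 × 8 / 2 = 36 such pairs. For one pair, (later − 1.2 × earlier) is normal with mean −0.2L and variance s²(1 + 1.44 − 2.4ρ). With s = 1 the SD is 1.562 for ρ = 0 and 1.114 for ρ = 0.5.

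- L = 10, ρ = 0: P(Z > 2/1.562 = 1.28) = 0.100 per pair.
- L = 20, ρ = 0: P(Z > 4/1.562 = 2.56) = 0.0052 per pair. Times 36, this is at most 0.19.
- L = 25, ρ = 0: P(Z > 5/1.562 = 3.20) = 0.0007 per pair. Times 36, this is at most 0.025.
- L = 15, ρ = 0.5: P(Z > 3/1.114 = 2.69) = 0.0035 per pair. Times 36, this is at most 0.13.

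The pairs overlap, so these products are upper bounds. Simulation gives the exact rates.

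**Simulated chance of at least one false progression by month 24, unrounded readings.**

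| Residual | s = 1 mm, independent | s = 1 mm, correlation 0.5 | s = 0.5 to 1.5 mm, independent |
|---|---|---|---|
| 10 mm | 83% | 50% | 12% to 97% |
| 15 mm | 43% | about 9% | 0.2% to 83% |
| 20 mm | 12% | 0.5% | 0% to 57% |
| 25 mm | 2% | below 0.1% | 0% to 30% |

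Rounding readings to whole millimetres raises the rates. At s = 1 mm with independent errors they become 91%, 53%, 16% and 2.5% at 10, 15, 20 and 25 mm.

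**Adding a minimum increase of 5 mm.** With independent errors and s = 1 mm, the rate falls to about 0.7% unrounded and 2.6% with whole-millimetre readings. At s = 1.5 mm, for residuals up to 25 mm, about 20% and 32% remain. The floor binds only where the nadir is below 25 mm, because 20% of 25 mm is already 5 mm.

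**The case against.** The strongest reply is that this is a declared summary of RECIST in a condensed article. The full protocol may name a version, a floor or a repeat-scan rule. That stands as a reason for modesty. It does not remove the point, because the article prints a complete threshold and reference, and followed as written they have the effect shown. The citation does not settle the version either, since the same reference number also supports the organ-at-risk dose limits.

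Four further objections hold in full or in part:

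- **Link to the endpoints.** The section "Progression-free survival" counts recurrence or progression anywhere and does not name the 20% rule. A reader might infer that this rule drives every progression event. The article does not say so, and new lesions and unequivocal non-target progression also count.
- **Size of nadirs.** The "Discussion" reports that "most patients achieved a PR or CR", and a reader might infer that nadirs here will mostly be small. That sentence concerns the earlier trial of carbon ions alone and gives no sizes. A fall from 40 to 28 mm is already a partial response, and a complete response leaves no diameter to misread.
- **Fragile rates.** Correlated errors cut the 15 mm figure from 43% to about 9%. Clinical override of an isolated small change would lower the rates further.
- **Confirmation.** It is tempting to call the missing repeat scan an error and to require the next 3-monthly MRI. That would need rules for death, salvage treatment or a missed scan before confirmation; without them, real progressions could go uncounted.

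**Conclusion.** The point holds in limited form. As printed, the rule lets reading error alone score progression on residuals of about 15 mm or less. With an error SD of 1 mm, the false rate by month 24 is about 83% at 10 mm and 43% at 15 mm under independence, about 50% and 9% with correlation 0.5, and about 2% or less from 25 mm. Larger error would extend the problem to larger lesions.

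A reader might conclude that the trial will record many false progressions. The document does not support that, because it states neither residual size nor reading error, and the outcome runs from near 0% to near 100% across plausible values. The downward bias in the secondary endpoints is conditional on this rule being the one that dates progression. Dose-limiting toxicity, 2-year overall survival, the sample size and the decision rule do not use it. Severity: minor.

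**What to change.** For endpoint scoring, define target-lesion progression as an increase of at least 20% and at least 5 mm over the smallest sum of longest diameters since treatment started. Let a new lesion, unequivocal non-target progression or pathologically proven recurrence count at once. Add one line saying whether this rule dates local progression-free survival and local control. Confirmation on the next scan need not be mandatory; it can serve as a sensitivity analysis.

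The cost is a change of wording, with no extra scans. True regrowth of under 5 mm would be called a visit or two later. The 5 mm figure is a proposal that the article itself does not support, and it does not remove all false calls if reading error is near 1.5 mm. The change concerns scoring only and leaves treatment decisions at progression as the article has them.
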